**Fig 2 pone.0326149.g002:**
[figure not shown]
Sequence of Experimental Visits. Following the baseline visit (*black* box), participants will be following the sequence of experimental visits shown here. Experimental sessions designed to manipulate exercise duration (*blue* boxes) will be conducted on the treadmill for: 1.) 10 min, 2.) 20 min, 3.) 30 min, and 4.) 60 min at a fixed exercise intensity of V̇O_2 _= VT1–15%. Experimental sessions designed to manipulate exercise intensity (*green* boxes) will consist of variable intensity treadmill walking/running at V̇O_2 _= 1.) VT1-30%, 2.) VT1-15%, 3.) VT1, and 4.) VT1 + 15% for a fixed duration of 30 min. Modality manipulation (*red* boxes) will include up-right cycling for 30 min at V̇O_2 _= VT1-30% and VT1-15%. * = Direct comparisons to examine differential biochemical responses to running/walking and cycling exercises. VT1 = The first ventilatory threshold.

For each experimental session, participants will report to the laboratory between 7 am and 12 pm following an overnight fast and caffeine intake abstinence. To control for circadian rhythm, all sequential experimental visits for each participant will be scheduled at the same time of the day. Upon arrival, participant body mass and body composition (BC 545, Tanita, Japan) will be recorded. Prior to exercise, an 18–22-gauge medical grade intravenous catheter will be inserted in the most easily accessible superficial peripheral vein at, or distal, to the antecubital fossa. An initial blood sample will be collected immediately prior to exercise initiation. A 5-min warm-up will then be performed at VT1–30% for all experimental sessions performed on the treadmill, or at a gradual intensity starting at 0 W and increasing up to the intensity eliciting the targeted V̇O_2_ for sessions performed on the cycle ergometer. After the 5-min warm-up, the targeted intensity will be maintained for the specific duration of the experimental sessions (i.e., 10–60 min). Immediately at exercise completion, a second blood sample will be collected. Participants will then recover for 60 min prior to the collection of a final blood sample. During the recovery period, all participants will remain seated within the facility and will remain fasted.

### Spirometry

Parameters reflective of pulmonary flows and volumes (FVC, FEV_1_, FEV1/FVC ratio, forced expiratory flow between 25% and 75% of vital capacity (FEF_25–75%_) and peak expiratory flow (PEF)) will be obtained (Quark CPET, COSMED, Italy) in accordance with international standards [35]. Flow–volume tracings from the best of a minimum of three FVC maneuvers will be retained.

### Cardiopulmonary exercise testing

Gas exchange and ventilation parameters will be measured using a commercially available medical grade metabolic cart (Quark CPET, COSMED, Italy). Heart rate will be continuously recorded using a commercial chest strap (Polar H10^TM^, Polar, Finland). The gas analyzer will be warmed up for 30 min and then calibrated according to the manufacturer guidelines. V̇O_2peak_ will be defined as the highest 20-s rolling average value recorded during the incremental cardiopulmonary test [36]. The highest heart rate value recorded will be considered the maximal heart rate (HR_max_). VT1 will be independently determined by two experimenters as the point at which CO_2_ production (V̇CO_2_) increases disproportionately compared to V̇O_2_, marked by a shift in the V̇CO2-V̇O_2_ slope from <1 or 1 to >1 [37]. Confirmation of VT1 will further be confirmed by subsequent evaluation of the relationships between ventilation (V̇E) and workload, V̇E/V̇O_2_ and workload, and P_ET_O_2_ and workload [38,39].

### Blood collection, preparation, and storage

Prior to each exercise session, an 18–22-gauge medical grade catheter (IN400600, BD Venflon^TM^ Pro Safety, BD, NJ, USA) will be inserted in the most easily accessible superficial peripheral vein at, or distal, to the antecubital fossa. During each experimental visit, blood samples will be collected immediately before exercise, immediately after exercise, and after 60 min of passive recovery from exercise. At each time point, approximately 4 mL of blood will be collected for plasma preparation and approximately 4 mL of blood will be drawn for serum preparation. Serum samples will be collected in tubes coated with a clotting activator gel (#01.1602, S-Monovette^®^ Serum Gel CAT, Sarstedt, Germany) and plasma samples in tubes coated with EDTA K3E (# 01.1605.001, S-Monovette^®^, Sarstedt). Tubes will be gently inverted ten times promptly after blood collection. Immediately after collection and prior to centrifugation, plasma tubes will be placed on ice for ∼10 min, while serum tubes will be kept for at least 30 min at room temperature. Both plasma and serum samples will be spun at 2,500 g for 10 min at room temperature. Supernatants will then be aliquoted in 200 μL vials and placed on ice for a maximum of 120 min prior to being stored at −80°C for follow-up analyses. We anticipate that approximately 10 vials of plasma and 10 vials of serum will be placed in frozen storage for each participant time point.

### Data analysis

#### “Omics” analyses.

Multiple *omics* platforms will be used to generate a comprehensive roadmap of the human biochemical exercise dose-response. Specifically, broad-base proteomic, metabolomic, lipidomic and transcriptomic analyses will be performed on plasma samples acquired at each experimental time point. Changes in protein abundance will be determined using liquid chromatography high-field asymmetric-waveform ion-mobility spectrometry tandem mass spectrometry (LC-FAIMS-MS/MS; Thermo Scientific Orbitrap Exploris 480, Thermo Fisher Scientific, California, USA) operated in Data Independent Acquisition mode. Changes in metabolite and lipid levels (i.e., concentrations) will be measured using chromatography – electrospray ionization tandem mass spectrometry approach (LC-ESI MS/MS) in a timed, selected reaction monitoring – t-SRM mode (TSQ Altis Plus, triple-stage quadrupole mass spectrometer, Thermo Fisher Scientific). The metabolite extraction and profiling will be done separately (using separate plasma aliquots) depending on the metabolite/lipid class, and using validated high-coverage targeted methodologies developed within the Metabolomics and Lipidomics Platform of the Faculty of Biology and Medicine of the University of Lausanne [40]. Amino acid, acylcarnitine and steroid quantification will be done using multiple-point calibration with internal standard spike. For complex lipids (~800 species belonging to five major classes including glycerolipids, cholesterol esters, sphingolipids, glycerophospholipids and free fatty acids), the estimated concentrations will be measured using single-point calibration with internal standard spike (75 IS at known concentration using Ultimate Splash mixture, Avanti Lipids) [41]. Transcriptome profiling will be performed using RNAseq technology [42].

#### Statistical analyses.

The Biomedical Data Science Center of the University of Lausanne and the Lausanne University Hospital (Lausanne, Switzerland) will oversee and coordinate all statistical analyses. It is anticipated that this work will generate a large database which will be amenable to conventional biostatistics and to rapidly evolving machine learning techniques. The theoretical basis for the following analyses is shown in Fig 3. Briefly, we hypothesize that measured molecules will conform to one of three specific response profiles: 1) up-regulated molecules, 2) down-regulated molecules, and 3) non-responsive molecules. Among molecules significantly up- or down-regulated by exercise, we further hypothesize that most will exhibit a distinct dose-response pattern, characterized either by a monotonic relationship (e.g., a linear correlation between molecular plasma concentration and exercise intensity and/or duration) or a threshold response. Threshold responsive molecules are anticipated to be unresponsive to low intensity and/or short duration intensity with subsequent up- or down-regulation occurring only in response to higher doses of exercise.

**Fig 3 pone.0326149.g003:**
[figure not shown]
Hypothetical molecular exercise dose-response profiles. It is anticipated that the majority of plasma-based molecules will adhere to one of 3 primary exercise dose-response profiles: *Unresponsive* to exercise (A), *Up-regulated* by exercise (B), or *Down-regulated* by exercise (C).

Conventional analyses that will be applied are summarized as follows. The primary goal of the HEI is to identify the exercise intensity and duration dose thresholds of molecular activation or down-regulation. Thus, the primary outcome will be the discrete exercise intensity and duration that produces a statistically different molecular concentration compared to resting baseline conditions. Each participant will undergo 10 discrete resting blood samples (i.e., one prior to each acute bout of exercise). The concentration of each molecule under resting conditions will be used to calculate a participant-specific mean and standard deviation baseline concentration for each molecule. Levels of each molecule will then be similarly measured again from samples obtained immediately and 60-minute after each discrete dose acute exercise session. This will facilitate the generation of immediate post exercise and 60-minute post exercise curves that plot molecular concentration on the Y-axis and exercise dose on the X-axis.

For each participant, the resting molecular concentration will serve as their unique, participant-specific y-intercept, while the rate of change (slope) for each molecule will be assessed during escalating exercise intensity and duration. Mixed-effects linear (or generalized linear) models will be used to identify molecules that significantly change with exercise dose, using slope as a proxy in linear regression, and to determine the precise exercise dose at which the curve deviates from zero. This approach will allow us to pinpoint which molecules respond to exercise and at what intensity or duration each responsive molecule is up-regulated (positive change) or down-regulated (negative change). The potential application of more advanced machine learning techniques (e.g., for dimensionality reduction, regularization, etc.) will be determined in collaboration with the biostatistics team at a later stage, based on the size and characteristics of the final dataset.

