A predefined sequence of exercise sessions will be applied for all participants (Fig 2). This sequence was implemented to ensure that: 1.) exercise sessions comprised of the higher exercise doses will be performed within the second half of the ten experimental visits, and that 2.) exercise sessions for which direct head-to-head comparisons are planned are not separated by more than one month (e.g., the two identical sessions performed at VT1–15% on the treadmill). To minimize the likelihood and/or impact of a physiologic training effect, consecutive visits will be separated by a minimum of 3 days and participants will abstain from any structured exercise training, above or below their pre-enrollment baseline level of habitual activity, outside of study visits for the duration of study participation.

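### Comparing every dose with a resting mean pooled over ten visits, under one fixed order with higher doses late, lets resting drift shared across participants and tied to visit order pass partly as a dose effect

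*Protocol article*

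**What the plan says.** All of this is in the protocol article.

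- **Resting samples** (Statistical analyses): "Each participant will undergo 10 discrete resting blood samples (i.e., one prior to each acute bout of exercise". They are then pooled: "The concentration of each molecule under resting conditions will be used to calculate a participant-specific mean and standard deviation baseline concentration for each molecule".
- **Role of the resting value** (same section): "the resting molecular concentration will serve as their unique, participant-specific y-intercept". The immediate and 60-minute concentrations are plotted against dose.
- **Primary outcome** (same section): "the discrete exercise intensity and duration that produces a statistically different molecular concentration compared to resting baseline conditions".
- **Model** (same section): "Mixed-effects linear (or generalized linear) models will be used to identify molecules that significantly change with exercise dose". The section presents this as a summary.
- **Order** (Experimental visits): "A predefined sequence of exercise sessions will be applied for all participants (Fig 2". One stated purpose is that "exercise sessions comprised of the higher exercise doses will be performed within the second half of the ten experimental visits".
- **Matched pre-sample** (Experimental visits): "An initial blood sample will be collected immediately prior to exercise initiation". This applies to each session.

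Experimental visits also lists safeguards. Visits are at least 3 days apart and outside training stays at its habitual level. Participants arrive fasted, at the same time of day, and sessions to be compared head to head fall within one month of each other.

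**The concern.** With a reference pooled over all ten visits, whatever shifts the resting level at one visit stays in that visit's post-exercise value and does not cancel. In a design with randomised or counterbalanced order, a common trend over visits would largely average out across doses. Here the order is the same for all, so it cannot. Early sessions are displaced one way and late sessions the other, and the late half is where the higher doses sit.

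The protocol itself points to causes that could follow visit number. Participants are sedentary to normally active and complete ten supervised bouts, and the visit spacing is justified as protection against a training effect. Any carry-over from larger bouts would also fall late.

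The primary outcome is at stake, because it is the dose at which a molecule departs from rest. So is the secondary aim of finding the minimal effective intensity and duration. Phase 1 is also meant to be the comparator for later cohorts, so a false threshold would be carried forward.

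**Working it through.** **1. The plan's own figure.** Sample size justification gives n = 20, two-sided alpha 0.05, ρ = 0.6 and more than 80% power for a 1.2-fold change (difference 0.20). It cites 1.44 ± 0.12 without saying whether 0.12 is an SD or a standard error, so the figure cannot be reproduced uniquely. A paired comparison has SD of change σ√(2(1 − ρ)) = σ√0.8.
- If 0.12 is the SD, power exceeds 99.9%.
- If 0.12 is a standard error from an assumed 8 to 20 source participants, power runs from 80% down to 42%.
- Power of 80% at 0.20 needs σ ≈ 0.339, so the SD of change is 0.339 × √0.8 = 0.303.

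I use σ = 0.339 below. This is an assumption that reads the stated lower bound as exactly 80%.

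**2. Bias from the pooled reference.** The mean visit number over ten visits is 5.5. With linear drift d per visit and no exercise effect, a sample at visit k is displaced by d × (k − 5.5).

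| Visit | d = 1% | d = 2% | d = 3% |
|---|---|---|---|
| 6 | 0.5% | 1% | 1.5% |
| 8 | 2.5% | 5% | 7.5% |
| 10 | 4.5% | 9% | 13.5% |

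Visits 1 to 5 mirror this with a negative sign. The drift values are assumed; the protocol gives none. They amount to 9, 18 or 27% from visit 1 to visit 10.

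**3. Variance of each contrast.** Let ρb be the correlation between samples from different visits and ρw the correlation within a visit.
- Post minus ten-visit mean: σ²(1.1 − 0.9ρb − 0.2ρw).
- Post minus same-visit pre: 2σ²(1 − ρw).
- With both correlations at 0.6: σ²(1.1 − 0.54 − 0.12) = 0.44σ² against 0.80σ². The ratio of standard errors is √(0.80/0.44) = 1.35.
- Setting the two equal gives ρw = (1 + ρb)/2, which is 0.8 when ρb = 0.6. Both are then 0.40σ².

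**4. False-positive rate for a single dose.** With the pooled reference, SE = 0.339 × √0.44 / √20 = 0.0503. The noncentrality is the bias divided by 0.0503, on 19 degrees of freedom. At visit 10 with d = 2%, for example, 0.09/0.0503 = 1.79, which gives 40%.

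| Visit | d = 1% | d = 2% | d = 3% |
|---|---|---|---|
| 6 | 5% | 5% | 6% |
| 7 | 6% | 9% | 14% |
| 8 | 8% | 16% | 29% |
| 10 | 14% | 40% | 72% |

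**5. Simulation check.** The assumptions were n = 20, no exercise effect, SD 0.27 of baseline, ρb = 0.6, ρw = 0.8, three illustrative visit orders and 1,500 runs per cell.
- Pooled reference, total drift 10%: false-positive rate 7–24% at the top dose and 13–40% for the dose slope.
- Pooled reference, total drift 20%: 12–71% and 36–93%.
- Same-visit reference: 3.5–7.1% throughout.
- No drift: both references hold about 5%.

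**The case against.** Averaging ten resting samples is a defensible way to gain precision. By the formulas above it has the smaller variance when same-visit samples are no more alike than samples from different visits. The safeguards are real and may keep drift small, and with no drift the pooled reference is valid. The model is only summarised, and visit terms or random-effect structure are commonly left to a fuller analysis plan, so their absence is not held against the protocol. All of that stands. What remains is that the protocol does fix the pooled mean as the reference, although each session has a matched pre-sample.

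A reader might also infer three stronger things that the document does not support.

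- **Any drift biases the result.** Only drift shared across participants and aligned with visit order does so. Recruitment and data collection run from October 2024 to July 2025. If starts are staggered, season and hormonal-cycle phase need not line up with visit number and would mainly add noise.
- **Dose rises at every visit.** The text says only that the higher doses fall in the second half. The order is in Fig 2, whose graphic was not in the text available for this check. Visit 10 is the worst position, and visit 6 shows almost no inflation.
- **The pooled mean discards the correlation used for power.** Sample size justification describes ρ generally, as correlation between repeated measures, and does not say which resting baseline is meant. The pooled mean comes from the same participant and keeps a correlation with the post sample.

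**Conclusion.** The point holds in a limited form. The pooled reference and the single fixed sequence together confound dose with any resting-level drift that is common to participants and follows visit order. This affects the primary outcome, and the conduct safeguards do not remove it from the analysis.

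The size is conditional. At visits in the second half, the single-dose false-positive rate could range from the nominal 5% to 72% under the assumed drifts of 1 to 3% per visit. It also depends on which session falls at which visit and on the assumed noise; a smaller SD would raise the rates. These figures illustrate sensitivity and do not predict what the study will see. The change is worth making because it is cheap and uses data already being collected.

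**What to change.** State that the primary contrast for each dose is the post-exercise value, and separately the 60-minute value, minus the pre-exercise value from the same visit. One way is a mixed model of all 30 samples per participant with:
- session (dose) main effects, time (pre, post, 60 minutes) and session-by-time terms as fixed effects;
- a participant random intercept and a participant-by-visit random intercept.

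The session main effects are needed. A numeric visit trend with a visit-level random intercept would not by itself make each dose effect equal to post minus same-visit pre.

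Keep the ten resting samples for the within-person SD and for a direct test of drift over visits. Report the pooled-mean reference as a sensitivity analysis.

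**Cost.** Analysis wording only, with no new visits or samples. The contrast's standard error rises by up to about 35% if same-visit samples correlate no more than samples from different visits (0.6). It is equal or smaller once same-visit correlation reaches 0.8, with between-visit correlation at 0.6.

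**What it does not solve.** If responsiveness to exercise itself changes over the visits, that change stays confounded with dose under the fixed sequence. This should be stated as a limitation.

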### Study aims

The primary aim of the HEI is to generate a comprehensive biochemical roadmap detailing the human dose-response relationship between exercise and molecular activation. The HEI protocol presented in this report will first be completed with young, sedentary to normally active people, without comorbid diseases. Comprehensive blood profiling will facilitate the identification of circulating blood molecules within major biochemical molecular families (i.e., proteins, polar, moderately polar and lipid metabolites, non-coding RNAs) that are up- or down-regulated by acute bouts of exercise. Secondary aims include: 1.) the determination of the minimal intensity and duration of exercise required to induce a statistically significant change in blood concentration of exercise responsive molecules, 2.) the characterization of dose-response kinetics profiles for responsive molecules, 3.) the identification of immediate *versus* late molecular responses (i.e., molecules up- or down-regulated immediately post exercise *versus* the 60-minute recovery time point) and, 4.) the identification of sex-based differences in the exercise-dose biochemical response.

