**Fig 1 pone.0326149.g001:**
[figure not shown]
Experimental Visit Exercise Dose Protocol. Participants will perform a total of 10 experimental visits. N = 4 will be dedicated to the manipulation of exercise duration (i.e., variable duration at a constant intensity, *blue* box), N = 4 will be dedicated to the manipulation of exercise intensity (i.e., variable intensity at a constant duration, *green* box), and N = 2 will examine the impact of differential exercise modalities (i.e., up-right cycle ergometer, *red* box).

The four pre-specified exercise intensities will be defined as the speed and incline, individualized and confirmed for each participant during the baseline visit, required to elicit a percentage of V̇O_2_ at the first ventilatory threshold (VT1) as follows: 1.) V̇O_2_ of 30% below VT1 (VT1–30%), 2.) V̇O_2_ of 15% below VT1 (VT1–15%), 3.) V̇O_2_ of VT1, and 4.) V̇O_2_ of 15% above VT1 (VT1 + 15%). These intensities were chosen to ensure that each participant would be capable of completing at least 30 min of continuous exercise at the three lowest intensities. During the VT1 + 15% visit, participants will exercise to the point of volitional exhaustion. It is anticipated that the majority of participants will reach exhaustion within 30 min under these conditions. In cases where this does not occur, the incline of the treadmill will be gradually increased to ensure that exhaustion is reached within 5 additional minutes.

The four sessions dedicated to the modification of exercise duration will be comprised of fixed intensity exercise at VT1–15% for sessions of 10, 20, 30 and 60 min. This intensity was chosen to ensure that each participant will be capable of completing the longest duration session of 60 min. To examine differential biochemical responses as a function of exercise modality, participants will complete two 30-min sessions on an up-right cycle ergometer at a cadence of 60–80 revolutions per min, each performed at a V̇O2 corresponding to −30% and −15% of treadmill-assessed VT1. Gas exchange will be monitored during the first 5–10 min to ensure that the target V̇O_2_ is reached within 5–6 min. Each session will begin with a continuous 1 W/s ramp until 80% of the target V̇O_2_ is reached, after which individualized manual adjustments will be made to achieve the final workload that correlates with the desired V̇O_2_.

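### On the immediate-post curve, bout duration and time since exercise onset rise together, so a plasma lag of about 20 min or more would be read as a minimal duration

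*Protocol article*

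**What the plan says.** All references are to the protocol article.

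- **Outcome (Statistical analyses).** The primary goal is to find the dose thresholds of molecular activation or down-regulation, and "the primary outcome will be the discrete exercise intensity and duration that produces a statistically different molecular concentration compared to resting baseline conditions". No sampling time is attached.
- **Analysis (Statistical analyses).** The plan builds "immediate post exercise and 60-minute post exercise curves that plot molecular concentration on the Y-axis and exercise dose on the X-axis" and uses mixed-effects models to "determine the precise exercise dose at which the curve deviates from zero".
- **Duration axis (Experimental visits).** Intensity is held at VT1–15% "for sessions of 10, 20, 30 and 60 min".
- **Timing (Experimental visits).** "A 5-min warm-up will then be performed at VT1–30% for all experimental sessions performed on the treadmill". Then: "Immediately at exercise completion, a second blood sample will be collected". The last sample follows 60 min of seated recovery.
- **Aims (Study aims).** Secondary aim 1 is "the determination of the minimal intensity and duration of exercise required to induce a statistically significant change in blood concentration". Secondary aim 3 separates immediate from late responders, so delayed molecules are expected.
- **Use (Discussion).** The thresholds are to be read as the duration needed for regulation, to inform doses in later studies and interventions, and to serve as the comparator for later cohorts.

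**The concern.** Each duration has one post sample, and it is taken when the bout stops. A longer bout therefore also gives the molecule more time to appear before sampling. If a 10-min bout is enough to trigger a molecule that takes 20 to 30 min to reach plasma, the short sessions look null and the long ones positive. This is the pattern that the Statistical analyses section calls a threshold response, yet here it reflects latency only.

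A mixed model with a slope for duration does not help, because duration and elapsed time are fully aliased in the post samples. A resting control would not remove the problem either, since the delay belongs to the response and is not background drift.

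At stake is the meaning of a main output. A delayed responder could be listed as needing a longer bout than it does, and that value would carry into later cohorts and intervention doses.

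**Working it through.** **1. The plan's own figure, which bounds the spread.** Sample size justification gives n = 20, two-sided alpha 0.05, ρ = 0.6, BDNF 1.44 ± 0.12 fold, and more than 80% power at 1.2 fold. It does not say whether 0.12 is an SD or a standard error.
- Read as an SD: SD of change = 0.12 × √(2 × (1 − 0.6)) = 0.107. The paired t-test then has power of about 100% at 0.20, which agrees with the stated bound.
- The largest SD of change that still gives 80% power is 0.303.
- I therefore use 0.107 to 0.303, with 0.20 between.

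**2. Time from onset to sample** (onset = start of the 5-min warm-up).
- Post: 5 + duration = 15, 25, 35, 65 min.
- Recovery: 65 + duration = 75, 85, 95, 125 min.

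**3. Without noise.** Suppose every bout triggers the same response, which appears L min after onset. The post curve first shows it at the 20-min bout for L = 20, at 30 min for L = 30 and at 60 min for L = 45. The 60-min curve shows it at 10 min in all three cases. The error begins once L exceeds 15 min (10 min if onset is counted from the target intensity).

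**4. With noise (assumed kinetics).** Response = 0.44 × (1 − exp(−(t − L)/τ)) for t > L, otherwise 0. The plateau is the plan's BDNF value; L and τ are assumptions. For L = 20, τ = 20 the mean rises on the post curve are 0, 0.10, 0.23 and 0.39. The table gives the first duration with p < 0.05 on the post curve (20,000 trials, paired t per dose, sessions independent).

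| L / τ (min) | SD 0.107 | SD 0.20 | SD 0.303 |
|---|---|---|---|
| 5 / 15 | 10 min: >99% | 10 min: 99% | 10 min: about 85% |
| 10 / 15 | 10 min: >99% | 10 min: 75%; 20 min: 25% | 10 min: 42%; 20 min: 57% |
| 20 / 20 | 10 min: 5%; 20 min: 92%; 30 min: 3% | 10 min: 5%; 20 min: 52%; 30 min: 43% | 10 min: 5%; 20 min: 26%; 30 min: 62% |
| 30 / 20 | 10 min: 5%; 30 min: 87%; 60 min: 3% | 10 min: 5%; 30 min: 48%; 60 min: 42% | 10 min: 5%; 30 min: 25%; 60 min: 65% |

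The 60-min curve reads 10 min in more than 99% of trials in every cell. The 5% in the last two rows is simply alpha: the true mean at the 10-min post sample is zero, so those hits are false positives.

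**5. Cross-check with another model.** A step response, the mean of ten resting samples as baseline, SD 0.30 per measurement, ρ = 0.6 and 3,000 runs also miss the 10-min threshold in about 95% of runs for lags of 20, 30 and 45 min.

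**6. Intensity axis.** The bouts are nominally 30 min, so time since onset is roughly constant, apart from the VT1 + 15% bout run to exhaustion. A lag there would tend to hide a response at every intensity and would not create a graded threshold.

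**The case against.** Several points on the other side stand.

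- **Two curves are intended.** A reader might infer that one primary outcome read from two curves is a contradiction. The documents do not support that: secondary aim 3 calls for both time points, thresholds that differ between them are part of its result, and which curve governs can be left to a statistical analysis plan.
- **The late samples are used.** A reader might infer that the 60-min samples of the short sessions go to waste. They are the first points of the planned 60-min curve, which would expose the delayed responder. A wrong duration is reported only if the post-curve value is interpreted without that curve.
- **The outcome is worded as concentration.** A post-curve threshold is correct for concentration at the end of exercise. It misleads only when read as the dose of activation or the duration needed, but the Statistical analyses and Discussion sections do read it that way.
- **The size is assumption-bound.** Lag, time constant and the all-or-none trigger come from outside the documents. At SD 0.107 the reported durations fall one dose step below those at SD 0.303, and the 10-min-lag case vanishes. The simulation also tests each dose separately, whereas the plan uses mixed models.
- **A joint test of both samples as the primary definition is debatable.** There is no resting control session, so drift over an hour of seated fasting could itself produce a 10-min threshold.

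What survives is the aliasing. It follows from the sampling times alone, and naming a governing curve does not remove it if the post curve is chosen.

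**Conclusion.** The concern holds for the duration axis of the immediate-post curve. For a molecule that any 10-min bout triggers but that appears 20 to 30 min after onset, the post curve finds the true 10-min threshold in about 5% of trials across SDs of change from 0.107 to 0.303. Whether it reports 20, 30 or 60 min instead depends on the assumed lag and SD, so no single wrong value should be quoted as the expected one. With lags of 10 min or less, the bias is small or depends on the SD.

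The documents do not show how many molecules have such lags; secondary aim 3 only shows that late responders are anticipated. One might also infer that the 60-min curve errs the other way for fast-clearing molecules. That is plausible but was not quantified.

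**What to change.** In the Statistical analyses section:

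1. Report each duration threshold by sampling time.
2. Call the post-curve value the *shortest duration with a change detectable at the end of exercise*.
3. Claim a minimal duration required for activation only when the 60-min samples of the shorter bouts also show no change from rest. Otherwise label the molecule a delayed responder whose minimal duration is at or below the shorter bout.
4. Optionally add a joint test of the post and 60-min samples at each dose as a sensitivity analysis.

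Two caveats belong in the text. The 60-min sample has no resting control, so a change there after a short bout may include drift; this applies to steps 3 and 4. The check also cannot see lags beyond 75 min, when the 10-min bout's last sample is drawn. Comparing that sample (75 min after onset) with the 60-min bout's post sample (65 min) is only approximate, because the times differ and one follows an hour of seated recovery.

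No new samples or visits are needed. The price is that some molecules will carry a less definite duration threshold.
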